#### Implementation study

Recruitment for participation in the implementation science portion of the study for clinic staff will take place in the intervention clinics once all participants have reached their 6-month post-ART timepoint and the cash transfer period (of 6 months) has ended. We will purposefully select staff from all study clinics such that our interviews include all levels of staff impacted by the changes in the clinic as related to implementation of the intervention (e.g., nurses, registration staff, physicians, In-Charges, pharmacists). Similarly, patients who have consented to and enrolled in the study will be purposefully sampled to assess their experiences with the cash transfer program and the mHealth system after their completion of cash transfer eligibility at 6 months. Specifically, we will interview patients who (a) received all six cash transfers, (b) received three or fewer of the six possible transfers, (c) enrolled in mobile money as a result of the study, (d) were virally suppressed at 6 months, and (e) were not virally suppressed at 6 months in addition to ensuring representation of both men and women and a range of ages.

### Outcomes and data collection

#### Primary outcome measure (impact evaluation, objective #1)

The primary endpoint is viral suppression at 12 months, defined as the proportion of PLHIV retained in HIV primary care and with suppressed HIV viral load 12 months after starting ART. The primary outcome is expressed as a binary variable, defined as PLHIV who are on ART and with sufficient HIV viral suppression (< 1000 copies/ml, WHO’s threshold for virologic failure in low- and middle-income countries [48]) versus not on ART or viral failure (≥ 1000 copies/ml). This outcome definition reflects global “treatment as prevention” strategies including the UNAIDS 95–95–95 targets, which aim for at least 95% of PLHIV to be on ART and 95% of those on ART virally suppressed. Patients considered not on ART include those who died, stopped ART and/or disengaged from care, or have not apparently received ARVs for ≥ 28 days since their last missed pharmacy pick-up [i.e., are lost to follow-up (LTFU)] following PEPFAR Monitoring, Evaluation, and Reporting Indicator Reference Guide Version 2.3 for current ART [49].

#### Secondary outcome measures (impact evaluation, objective #1)

Viral suppression (< 1000 copies/ml) at 6 months;Retention on ART at 6 and 12 months;The proportion virally suppressed of those retained on ART at 6 and 12 months; andAppointment attendance, the proportion of scheduled visits that were completed during the 0–6- and 0–12-month periods.

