To address these questions, we are employing an implementation science approach to evaluate a cash incentive program designed to promote ART adherence among PLHIV in the Lake Zone, Tanzania. Over the past several years, our team has designed and conducted a set of iterative experiments to determine the *efficacy* of the incentive-based intervention, *optimize* the intervention for a real-world clinical setting, and assess the feasibility and acceptability of the intervention package for scale-up and sustainability. The effectiveness trial described in this protocol is the logical next step in evaluating incentive-based approaches for improved HIV care outcomes. Together, this set of trials (efficacy–optimization–effectiveness) will generate an evidence base for the most effective, incentive-based implementation strategy for the clinically proven intervention of ART adherence.

Results from the first two randomized trials conducted by our team (efficacy and optimization) demonstrated that cash transfers conditional on visit attendance have the potential to improve ART adherence and retention in care among PLHIV in Tanzania. In the first study (efficacy), our team randomized 800 food-insecure PLHIV who recently started ART at three clinics to the standard of care or 6 months of cash or food transfers, conditional on visit attendance [24]. After 6 months of the intervention, we found that short-term cash transfers were superior to the standard of care on all indicators of adherence and retention, including the medication possession ratio (MPR), a pharmacy-based measure of adherence associated with viral suppression [25–28], appointment attendance, and loss to follow-up [20]. At 12 months, 6 months *after* the *intervention ended*, the cash group remained more likely to be in care than the standard of care group and had superior appointment attendance. Furthermore, cash transfers were safe to administer [29, 30] and, compared to food baskets, were equal or superior to food support on all outcomes, were cheaper and easier to monitor, and were preferred by patients. Analysis of individual motivation found that cash transfers do not undermine intrinsic motivation to adhere to HIV treatment; indeed, intrinsic motivation *increased* over time as PLHIV experienced the benefits of treatment [31]. Qualitative research revealed that money received as part of the intervention was largely being spent on food, school fees, and investment in assets and small businesses.

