#### Rationale for the cash amount and duration

Our now-completed study to optimize the intervention found that both cash transfer amounts (10,000 TSH and 22,500 TSH per month) significantly improved 6-month viral suppression versus the standard of care. At 6 months, we found a positive trend between incentive size and HIV viral suppression (OR = 1.10 per 2500 TZS, 95% CI 1.03 to 1.17). Further, we found that both cash amounts significantly improved HIV viral suppression over the comparison group [10,000 TSH 83% vs. 73%, risk difference (RD) = 10.2, 95% CI 1.6–18.8; 22,500 TSH 85% vs. 73%, RD = 12.1, 95% CI 3.6–20.6]; there was no significant difference between incentive groups (RD = 1.9, 95% CI − 5.8 to 9.7). However, only the larger cash value yielded significant improvements over the standard of care for the secondary outcomes of retention in care (RD = 7.1, 95% CI 0.3 to 13.9) and viral suppression among the subset retained in care (RD = 7.8, 95% CI 0.9 to 14.7). To determine the final cash transfer size for the current study, we followed our pre-registered analysis plan (at AsPredicted), as well as several additional analyses including a cost analysis; discussions with local stakeholders, including the Regional Medical Officers, and co-investigators; assessment of budgetary trade-offs associated with a smaller cash transfer versus larger study size; and consideration about the benefits and weaknesses of various cash amounts (including power considerations and the ethics of engaging in a statistically underpowered study; for example, powering the study for the smaller amount would require twice as many clinics in the study, or the study would be significantly underpowered). In addition, with expansion to additional regions, some with higher average levels of socioeconomic status than the region included in the optimization trial, there was some concern that the smaller transfer would be of lower value and thus not enough to improve adherence. Finally, the larger cash amount is of comparable magnitude to the monthly payments distributed through Tanzania’s social action fund, TASAF. After considering these factors, many of which are context-specific, we determined that the effectiveness evaluation will include a cash transfer amount of 22,500 TSH per month for 6 months.

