#### Data analysis—impact study

We will conduct an intent-to-treat analysis to determine the effect of the intervention on 12-month viral suppression (the primary outcome). We will conduct a cluster-based permutation test on the individual-level outcome data, which accounts for clustering within the clinic. The effect estimate of interest is the risk difference of viral suppression among PLHIV attending intervention versus comparison facilities. We will pre-register our analysis plan at AsPredicted.

We will conduct several secondary analyses of the primary outcome, although we are not powered for these analyses. We will examine heterogeneity in the primary analysis by facility and patient characteristics. We will also conduct a treatment-on-the-treated analysis to isolate the impact of incentive delivery [53–55].

Using the same methods as for the primary analysis, we will also assess effects on the following key secondary outcomes:
Viral suppression (< 1000 copies/ml) at 6 months;Retention on ART at 6 and 12 months;The proportion virally suppressed of those retained on ART at 6 and 12 months; andAppointment attendance, the proportion of scheduled visits that were completed during the 0–6- and 0–12-month periods.

We will additionally assess effects on the following survey-based outcomes at 6 and 12 months:
Food securityMental health (anxiety, depression)HopefulnessIPVSelf-efficacyParticipation in the labor force/functional statusOther indicators of household welfare (e.g., investment in small businesses)

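### Suppression among those retained on ART is analysed as an effect of cash, but retention is itself changed by cash, so this contrast may be selection-biased

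*Protocol article*

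**What the plan says.** The protocol article, under Secondary outcome measures (impact evaluation, objective #1), lists "The proportion virally suppressed of those retained on ART at 6 and 12 months". The same item is in the Design section and again in Data analysis—impact study, where it is introduced by "Using the same methods as for the primary analysis, we will also assess effects on the following key secondary outcomes". The primary method in that section is described as "We will conduct a cluster-based permutation test on the individual-level outcome data, which accounts for clustering within the clinic", and the estimate of interest is the risk difference between intervention and comparison facilities. The article gives this outcome no descriptive label and no caveat about its denominator.

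Retention on ART at 6 and 12 months is a separate secondary outcome in the same list. Two earlier trials by the same team indicate that cash moves it:

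- Rationale for the cash amount and duration says that only the larger amount improved the "secondary outcomes of retention in care (RD = 7.1, 95% CI 0.3 to 13.9").
- Background says of the efficacy trial at 12 months, six months after support ended, that "the cash group remained more likely to be in care than the standard of care group".

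The primary outcome is built differently. Participant tracing—impact evaluation states that patients not retained on ART stay in its denominator.

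**The concern.** The denominator of this outcome is fixed after randomisation by something the intervention is meant to improve. If cash keeps in care some patients who would otherwise have left, the retained group in the cash arm contains a kind of patient that is absent from the retained group in the control arm. A difference in suppression between the two groups then mixes any effect on suppression with a difference in who is being compared.

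The permutation test does not repair this. It is valid for the null hypothesis that cash changes nothing, retention included. If cash changes retention but not suppression in patients who would stay either way, the retained subsets are not exchangeable between arms, and a rejection cannot be attributed to suppression.

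What is at stake is how one key secondary outcome is read. The contrast could understate a benefit among patients in care, or overstate it, and it would be reported as a randomised effect.

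**Working it through.** **The plan's own figure.** The article gives no expected value for this outcome in the present trial. Its only design figure is the detectable difference of 11 points for all-enrolled suppression at 12 months. That figure reproduces. The design effect is 1 + (56 - 1) × 0.05 = 3.75, and the effective size per arm is 16 × 56 / 3.75 = 238.9. For 70% against 81% the power is 80.0% (16 clinics per arm and a two-sided 5% level are assumed). It says nothing about the retained-only contrast.

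**Inputs for the illustration.**
- e, the extra share retained because of cash: 0.071, CI 0.003 to 0.139 (Rationale for the cash amount and duration). It belongs to the earlier trial's 6-month results; using it at 12 months is an assumption, since Background supports only the direction at 12 months.
- R0, control retention: 0.83, assumed; the article does not give it.
- s0, suppression in patients retained either way: 0.85, assumed.
- q, suppression in the extra retained: assumed and varied.
- Cash is given no effect on suppression in patients retained either way, and it is assumed never to cause anyone to leave care.

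**Formula.** Retained-only suppression with cash = (R0 × s0 + e × q) / (R0 + e). In control it is s0. The difference is e × (q - s0) / (R0 + e), and all of it is selection.

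**Varying q, with e = 0.071:**

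| q | Cash arm, retained only | Difference from 85.0% |
|---|---|---|
| 0.85 | 85.0% | 0 |
| 0.70 | 83.8% | -1.2 points |
| 0.50 | 82.2% | -2.8 points |
| 0.30 | 80.7% | -4.3 points |

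If q exceeds s0, the sign reverses.

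**Varying e over its CI, with q = 0.50:**
- e = 0.003: 0.003 × (-0.35) / 0.833 = -0.1 points
- e = 0.071: 0.071 × (-0.35) / 0.901 = -2.8 points
- e = 0.139: 0.139 × (-0.35) / 0.969 = -5.0 points

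**Varying R0.** Hold control all-enrolled suppression at the article's 70% for 12 months, so that s0 = 0.70 / R0, and keep e = 0.071. For R0 from 0.75 to 0.90 the difference runs from -3.7 to -2.0 points at q = 0.50, and from -5.9 to -3.9 points at q = 0.25. At R0 = 0.85 and q = 0.50, retained-only suppression falls from 82.4% to 79.9%, while all-enrolled suppression rises by 0.071 × 0.50 = 3.55 points.

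**The case against.** The proportion suppressed among patients on ART is a recognised indicator; the article ties its outcomes to the UNAIDS targets. Listing it is reasonable. The primary outcome keeps everyone in the denominator, and retention is reported separately at both times. A reader would see all three results together and could detect a conflict between them. All of this stands, and it limits the consequence. It does not make the retained-only contrast a randomised effect, which is how the analysis section treats it. Endline tracing helps to classify silent transfers correctly, but patients who died, stopped ART or disengaged still leave this denominator.

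The article also says that an analysis plan will be pre-registered. That does not answer the point, because the article itself already chooses the method for this outcome.

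Three stronger readings are tempting and are not supported:

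- **That the trial will show false harm.** This is possible, not predicted. The earlier trial reported a positive contrast for "viral suppression among the subset retained in care (RD = 7.8, 95% CI 0.9 to 14.7"). Take that trial's 73% against 73% + 12.1 = 85.1% all-enrolled suppression, a retention gain of 7.1 points and an assumed control retention of 80%, 85% or 90%. Trimming bounds for patients retained either way are then 6.2 to 8.8, 5.9 to 14.1 and 5.6 to 13.4 points, before sampling error. They are all positive.
- **That the bias is a stated share of the expected signal.** Dividing 1.2 to 4.3 points by 7.8 would give 15% to 55%. But 7.8 comes from the same retained-only contrast and carries whatever selection it contains, so it is not a clean denominator.
- **That the survey outcomes fail in the same way.** The article says "We will additionally assess effects on the following survey-based outcomes at 6 and 12 months", and Data collection plans patient surveys with n = 1984, which is everyone enrolled. Nothing says that only patients still in care will answer. Handling non-response is commonly left to the analysis plan.

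**Conclusion.** The concern holds as a matter of interpretation for one key secondary outcome at 6 and 12 months. The article commits to assessing an effect on a subset defined by a post-randomisation outcome that its own earlier trials indicate cash changes. The contrast may be selection-biased. Under the stated assumptions the bias is -2.8 points at the point estimate of the retention gain and about -0.1 to -5.0 points across its CI, so it ranges from negligible to material.

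The sign and size rest on control retention and on suppression in the extra retained, neither of which the article gives. At 12 months they rest also on carrying over the 6-month retention gain. The primary conclusion, which counts all enrolled patients, is not affected.

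**What to change.** In Data analysis—impact study, take the retained-only proportion out of the list of effects assessed with the primary method. Report it by arm at 6 and 12 months as a descriptive step of the care cascade, next to retention and all-enrolled suppression. State that effect conclusions come from those two.

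If an effect among the retained is wanted, define it for patients who would be retained in either arm and give trimming (Lee-type) bounds. State the assumption these need: that cash never reduces any patient's retention.

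The cost is a change of wording and, if bounds are used, a few lines of code. Data collection does not change. The downside is that one key secondary outcome becomes descriptive or is reported as an interval of bounds.

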#### Primary outcome measures (implementation study, objective #2)

Implementation outcomes assessed through in-depth interviews and surveys with patients and clinical staff: adoption, acceptability, penetration, fidelity, feasibility, appropriateness, and sustainability, plus usability (Table 1).

**Table 1 Tab1:** Implementation study: data collection approaches and Proctor’s implementation science constructs

Data collection approach	Implementation outcomes	Outcome indicators
Patient survey (baseline, 6 months)	Adoption (mobile money)	Initiation of use of mobile money; satisfaction with the program generally and the mHealth system specifically
	Acceptability	
Clinical staff survey (6 months)	Acceptability	Staff support and acceptance, level of institutionalization
	Penetration	
	Fidelity	
	Feasibility	
In-depth interviews with clinic staff (6 months)	Acceptability	Staff support and acceptance, staff burden, practicality, and perceived fit
	Appropriateness	
	Sustainability	
In-depth interviews with patients plus usability survey (6 months)	Acceptability	Patient satisfaction with program and delivery model, impact on patient, practicality and perceived fit, adoption of mobile money
	Appropriateness	
	Adoption	

#### Data collection

Data collection will include the following:
Medical record review for the primary outcome, viral suppression, at 6 and 12 monthsSurveys with patients at intervention and control clinics at baseline and 6 and 12 months (*n* = 1984)In-depth interviews with patients in the intervention clinics at 6 months (*n* = 30)Surveys with clinical staff at intervention and control clinics at 6 months (*n* = 110)In-depth interviews with clinical staff at intervention and control clinics at 6 months (*n* = 40)

We linked each data collection activity for the implementation study to implementation outcomes in the Proctor et al. framework (Table 1) [34]. We will analyze data from structured surveys and in-depth interviews to examine the implementation constructs of acceptability, penetration, sustainability, appropriateness, adoption, feasibility, and fidelity. We will use validated surveys to assess the usability of the mHealth system from both the clinic staff and patient perspectives, including the System Usability Scale [50] and the Health Information Technology Usability Evaluation Scale [51].

#### Participant tracing—impact evaluation

As retention in care is included as part of the definition of the primary outcome of this study (i.e., those not retained on ART are included in the denominator of the primary outcome of viral suppression), no additional retention activities will be implemented other than the routine procedures already in place and led by clinical staff. According to national guidelines, patients who miss a scheduled appointment are tracked in the community by a system of home-based care providers (HBCs); this system will remain in place during the study. In addition, we will closely track implementation of patient tracking as specified in the national guidelines within each study clinic so that we can capture any variation in implementation at the clinic level. Research staff will not be involved in tracing participants at any study facility during the 12-month follow-up of each participant. At endline only (12 months), research assistants will enhance these procedures with additional robust tracing using “gold-standard” tracing methods (at least 3 tracing attempts using multiple methods), procedures to investigate all potentially LTFU patients, confirm “silent transfers” (those who transfer to new facilities without notification of the prior facility) and deaths, and refer patients to health facilities where missing plasma specimens can be collected by health facility staff for viral load quantification.

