#### Intervention arm

In addition to the mHealth system as described above, participants in the intervention arm will have the opportunity to receive up to 6 consecutive monthly cash transfers of 22,500 TSH (~ $10) each, conditional on visit attendance with the HIV care provider. Cash transfers will be given once monthly for *up to* 6 months, spaced ≥ 25 days apart (consistent with National Guidelines for monthly or bimonthly visits [43]). This means that the cash transfer is only given when the patient visits the clinic for their routine appointment, regardless of whether the visit is earlier or later than the scheduled appointment (but no earlier than 25 days since the last transfer). Upon the monthly visits when a patient checks in for their appointment (via fingerprint or entry of clinic ID), the cash transfer will be automatically distributed through the mHealth system. Transfer amounts are exclusive of transaction fees (< $1), which will also be included in the transfer. Thus, the intended amount is transferred to the patient upon withdrawal.

If a participant does not have a mobile money account, (1) s/he can sign up and return to the clinic on a different day to link this account to the mHealth system or (2) s/he may ask a trusted friend or relative to receive the transfer. Mobile money is a secure and convenient way for financial transactions, as mobile money kiosks are ubiquitous in the study regions and mobile phone ownership in Tanzania is high and approaching levels in the USA (75% in 2018 and rapidly increasing [45]). For participants who do not have mobile banking, wherever possible, we will make referrals to kiosks where they can sign up for the service, if desired. In the most recent study, we found that 88% of participants had access to a mobile phone and 79% had access to mobile banking.

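### Six-month retention and viral suppression are at risk of differential misclassification, probably in favour of cash, because silent transfers are actively confirmed only at 12 months

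*Protocol article*

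**What the plan says.** Under Participant tracing—impact evaluation, the article states: "Research staff will not be involved in tracing participants at any study facility during the 12-month follow-up of each participant". Until then, only the routine system operates, in which home-based care providers follow up missed appointments. The exception is the end of follow-up: "At endline only (12 months), research assistants will enhance these procedures with additional robust tracing". That step is meant to investigate everyone who may be lost to follow-up, confirm deaths and silent transfers (defined as "those who transfer to new facilities without notification of the prior facility"), and refer patients for missing viral load specimens.

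The secondary outcomes include viral suppression at 6 months and "Retention on ART at 6 and 12 months". The impact-study analysis section calls these key secondary outcomes and analyses them by the primary method. The Data collection section takes viral suppression at both time points from medical record review. The primary outcome definition counts as not on ART anyone with no apparent ARV receipt for 28 days or more after a missed pick-up, and the tracing section adds that "those not retained on ART are included in the denominator of the primary outcome of viral suppression".

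Under Intervention arm, participants may receive "up to 6 consecutive monthly cash transfers of 22,500 TSH", and "the cash transfer is only given when the patient visits the clinic for their routine appointment". Payment is triggered by check-in through the mHealth system, which is installed in the study facilities.

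**The concern.** Someone who starts ART at a study clinic, moves to another facility in month 4 without telling the first one, and keeps taking ART has not failed treatment. In the study clinic's records, though, that person looks lost. At 12 months the protocol actively corrects this. At 6 months it states no correction.

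Misclassification at equal rates in both arms would lower both proportions and leave little or no spurious difference. The worry is that the rates may differ. During months 0–6 a cash participant who leaves for a facility outside the study gives up the remaining transfers, worth up to 6 × 22,500 = 135,000 TSH in all. A control participant gives up nothing comparable. The protocol accepts that cash can influence where patients attend: it separates clinics by at least 15 km and withholds the existence of the two arms to discourage moves from control to intervention clinics. It does not discuss the reverse effect, cash holding patients at the clinic that pays them.

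At stake is the meaning of the two 6-month results. Part of an apparent gain in retention or suppression could reflect staying visible at the paying clinic rather than staying on treatment.

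**Working it through.** **The plan's own figure.** The article gives no silent-transfer rate and no precision figure for the 6-month outcomes. Its one related figure is the minimum detectable difference for 12-month suppression, which can be reproduced with 16 clinics per arm and two-sided 5% (both assumed):
- Design effect = 1 + (56 − 1) × 0.05 = 3.75.
- Effective n per arm = 16 × 56 / 3.75 = 238.9.
- 70% against 81% gives 80.0% power, matching the stated 80% and 11 points.

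This does not bear on the concern itself, but it supports using the same variance model below.

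**How a silent transferee is classified at 6 months, as written**
1. Silent transfer before month 6: no ARV pick-up is visible at the study clinic.
2. After 28 days without apparent ARVs: not on ART, so not retained.
3. Composite suppression: the participant stays in the denominator and counts as not suppressed. The denominator rule is stated for the primary outcome. I read it as applying to 6-month suppression too, because suppression among those retained is listed as a separate outcome.

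**Size.** Let tC and tI be the silent-transfer shares by month 6 in control and cash, r the share recovered by other means, and s the suppression among transferees.
- Retention bias = (tC − tI) × (1 − r)
- Suppression bias = (tC − tI) × (1 − r) × s

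The values of tC, tI and r are assumptions. For s I use two figures from the article as a range: 75.2% (phase I control group at 6 months) and 87% (people on treatment in Tanzania with a viral load result).

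| Control vs cash, r = 0 | Retention bias (points) | Suppression bias (points) |
|---|---|---|
| 2% vs 1% | +1.0 | +0.8 to +0.9 |
| 4% vs 2% | +2.0 | +1.5 to +1.7 |
| 10% vs 5% | +5.0 | +3.8 to +4.4 |
| 5% vs 5% | 0 | 0 |
| 3% vs 5% | −2.0 | −1.5 to −1.7 |

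For example, 10% vs 5% gives 5.0 × 0.752 = 3.76 and 5.0 × 0.87 = 4.35. Recovering half (r = 0.5) halves every entry. With 16 × 62 = 992 participants per arm, 1 point is about 10 participants and 5 points about 50.

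**Consequence for 6-month suppression if cash has no true effect.** Take 62 per clinic, ICC 0.05 (the 12-month value, carried over), control 75.2% and two-sided 5%.
- Design effect = 1 + 61 × 0.05 = 4.05; effective n per arm = 992 / 4.05 = 244.9.
- For a bias b, SE = √{[0.752 × 0.248 + (0.752 + b)(0.248 − b)] / 244.9}.
- The chance of a significant result favouring cash is Φ(b/SE − 1.96): 2.5% at b = 0, 4.4% at 1 point, 7.5% at 2, 12.0% at 3 and 26.5% at 5. The last lies just above the range in the table.

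**The case against.** The strongest reply is that the article shows only half of what is needed. Bias in favour of cash requires more undetected transfers in control than in cash, and no later correction of 6-month status. Neither is established. Endline tracing covers everyone potentially lost, so a month-4 transferee is within its scope. How its findings feed back to the 6-month outcomes is a derivation rule that may sit in the full protocol or the pre-registered analysis plan. There are also safeguards: people who intend to transfer within 12 months are ineligible, home-based tracking runs in both arms and its implementation is monitored, and patients in both arms are surveyed at 6 months. Withholding research tracing during follow-up is a deliberate choice for a trial meant to mirror routine practice.

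Much of this stands. A reader might infer that the 6-month outcomes are biased; the documents support only a risk, because equal transfer rates give no bias and the reverse pattern gives bias against cash. The safeguards reduce the risk but do not remove it: eligibility screens stated intent only, the survey is not named as a source of ART status, and the protocol itself still sees a need to confirm silent transfers at endline. The derivation rule could be left to an analysis plan, but the dates it needs must be captured when the tracing is done.

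Two further inferences should be resisted. Suppression among those retained is not affected in the same way, because an untraced transferee leaves both numerator and denominator. Nor does the text show that tracing at 12 months distorts the primary outcome by bringing lapsed patients back: ART status is already tied to ARV receipt, and nothing says that a return to care after contact changes it.

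**Conclusion.** The point holds as a conditional risk to two key secondary outcomes, 6-month retention and composite 6-month suppression. Silent transfers are actively confirmed only at 12 months, and the incentive to remain visible at the study clinic in months 0–6 exists in one arm only. The probable direction favours cash, on the plausible but unproven premise that cash reduces silent transfer.

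The size cannot be derived from the documents. Under the assumed range it is about 1 to 5 points in retention and 0.8 to 4.4 points in suppression, with no recovery. For scale, the optimization trial's 6-month retention effect at this cash amount was 7.1 points (95% CI 0.3 to 13.9), but that comparison sets an assumed figure beside an observed one. Recovery through home-based tracking or the 6-month survey would shrink the bias. The 12-month primary outcome is outside this point.

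**What to change.** Keep the tracing schedule as it is and use the planned endline tracing to correct the 6-month data:
- For every participant investigated, record the dates of transfer, death and ARV pick-up, including pick-ups at receiving facilities.
- Reclassify 6-month ART status from those dates.
- Use 6-month viral loads from receiving facilities where they exist. A 6-month specimen cannot be obtained at 12 months, so state how a participant reclassified as on ART but without a result is handled, preferably by the rule used for retained participants with no test.
- Report 6-month retention and composite suppression by arm with and without the correction, together with the number of silent transfers found in each arm.

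The cost is a few date fields on the tracing form and a short passage in the analysis plan, with no added tracing. The downside is that receiving-facility records will be incomplete for some patients, so the correction will be partial, and more so for suppression than for retention.
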